**Selection of Households:** Households to participate in the study will be recruited through a systematic sample from a subset of villages in Fulbaria selected based on field factors such as ease of transport and proximity to the field office. The inclusion criteria will include (1) using a shallow tubewell that is free from iron complaints as the bari’s primary source of drinking water and (2) having a child between the ages of six months and two years living in the bari. The primary caregiver in the household that has the child in the target range will be recruited into the study. If there are multiple households in the bari that have a child between the ages of six months and two years, one of the households will be randomly selected and the primary caregiver in the selected household will be recruited. Recruited households will be randomized into one of the three study arms by block randomization through a randomly generated, pre-established sequence that will determine which intervention will be allocated to the household.

**Promotion of Interventions:** The intervention will continue for ten months. At the first visit to the households, Groups 1 and 2 will be provided with a plastic water storage container with a lid and a narrow mouth/tap, and Group 1 will also be given a one-month supply of tablets. Households will be taught through demonstrations and a flipchart with illustrations how to use the tablets as well as how to properly use and clean the safe storage containers, and they will be encouraged to use them regularly. They will also be given an instructions sheet with illustrations that will be left at a visible spot in the household and serve as a reminder to clean the containers and if applicable add the water treatment tablets. A field research assistant who is not part of the evaluation team will visit the household once per month to encourage regular water treatment and safe storage, replenish the supply of tablets and address any issues with the maintenance and cleaning of the safe storage vessels. The rest of the protocol has been written assuming that households will receive monthly promotion visits. However, if the pilot study shows that more frequent, intensive promotion leads to significantly better uptake, in the full-scale study we will consider replacing the monthly promotion frequency with more frequent promotion visits.

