**Study Timeline:**

## Sample Size Calculation and Outcome (Primary and Secondary) Variable(s)

Study Arms:

1: Chlorine + Safe Storage

2: Safe Storage

3: Standard Practice

Hypothesis 1 (Main Hypothesis, Arm 1 vs. 3): Children who live in households that use tubewell water for drinking that is treated with effective chlorination and safely stored will have less diarrhea than households that use shallow tubewell water for drinking that is not treated and not safely stored.

Hypothesis 2 (Arm 1 vs. 2): Children who live in households that use tubewell water for drinking that is treated with effective chlorination and safely stored will have less diarrhea than households that use tubewell water for drinking that is safely stored but not treated with chlorine.

Hypothesis 3 (Arm 2 vs. 3): Children who live in households that use tubewell water for drinking that is safely stored but not treated will have less diarrhea than households that use tubewell water for drinking that is not treated and not safely stored.

While hypothesis 1 (the combined effect of chlorination and safe storage) is our main hypothesis, the study has been conservatively sized to have sufficient power to test hypothesis 2 (individual effect of chlorination), using the following assumptions:

- 2-day prevalence (as opposed to 7-day prevalence) used in calculations to be conservative
  - 14% longitudinal prevalence in Arm 3 (based on SHEWA-B data)
  - 11.6% longitudinal prevalence in Arm 2 (based on Roberts et al., 2001)
  - 9.1% longitudinal prevalence in Arm 1 (based on Arnold and Colford, 2007)
- 1 child between the ages of six months and two years per tubewell
- 5 follow-up visits per child
- 0.13 ICC and 1.50 design effect for repeated measures per child
- 10% drop-out
- One-tailed test with 95% confidence level

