We will assess the magnitude of the differences in longitudinal prevalence by group by calculating a risk ratio between the groups. We will evaluate if risk ratios differ from 1.0 at traditional testing levels (*P*=0.05) using robust standard errors that account for repeated observations within children (Zeger and Liang 1986). We will repeat the calculations using the longitudinal prevalence of diarrhea among children under the age of five as the outcome measure to allow us to compare our results to other findings from the literature that focus on children under five.

Secondary outcomes will include the proportion of households by group that have contaminated water as measured by H2S testing and by quantitative evaluation of total coliforms and *E. coli.* We will assess the proportion of samples within each group that have no evidence of contamination. We will compare whether these proportions are different than would be expected by chance using chi square when there are no repeated samples and using general estimated equations when repeated samples are analyzed from the same household.

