## Minor changes made to this protocol before study implementation:

1. Random subset of households in randomly selected villages (instead of systematic subset of households in villages close to the field office) to achieve representative random sample.
2. 180 households (60 from each study arm) tested for *E. coli* and total coliforms instead of 150 households (50 from each study arm) to achieve testing in 10% of study households.
3. MI Agar (Becton, Dickinson and Company, Maryland, USA) to enumerate *E. coli* and total coliforms instead of MI Broth (Whatman Inc, New Jersey, USA).
4. Digital colorimeter (Hach, Colorado, USA) to measure free chlorine residual instead of DelAgua kit to achieve increased precision.
5. Longitudinal prevalence in the protocol used to refer to period prevalence. Period prevalence measured to avoid inaccuracies associated with collecting diarrhea data for each day of the 7-day recall period.

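### The primary risk-ratio test is valid but uses neither village nor randomisation block; adjusting for village is a cheap gain in precision of uncertain, probably small, size

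*Protocol*

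**What the plan says.** **Allocation.** Research Design and Methods (Selection of Households): "Recruited households will be randomized into one of the three study arms by block randomization through a randomly generated, pre-established sequence". Block size, any stratification by village and the order of enrolment are not given.

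**Sampling.** The same paragraph draws households from a subset of villages. The list of minor changes made before implementation amends this to "Random subset of households in randomly selected villages". The number of villages is not given.

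**Unit.** Where a bari has several eligible households, "one of the households will be randomly selected and the primary caregiver in the selected household will be recruited". The sample size section assumes "1 child between the ages of six months and two years per tubewell". For the primary age group the child is therefore practically the randomised unit.

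**Primary test.** Data Analysis: risk ratios are tested against 1.0 at P=0.05, "using robust standard errors that account for repeated observations within children". The sample size likewise carries a design effect only for repeated measures per child (ICC 0.13, design effect 1.50). Neither section has a village or block term.

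**The concern.** When households are randomised within villages, whatever a village shares (source water, sanitation, field staff, time of enrolment) is spread across the arms and drops out of the arm contrast. A standard error that treats children as independent across villages still counts that shared variation as noise. Its intervals are then wider than the design warrants, and the test is conservative.

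The stake is precision. It matters most for Arm 1 vs 2, the contrast that isolates chlorination and on which the trial was sized, because that contrast has the least power to spare of the two for which the protocol states a power.

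**Working it through.** **Inputs from the protocol.** "9.1% longitudinal prevalence in Arm 1"; "11.6% longitudinal prevalence in Arm 2"; "14% longitudinal prevalence in Arm 3"; within-child ICC 0.13; 600 households per arm less 10% drop-out = 540; one-tailed 5% for sizing. Visits per child: m = 5 in the sample size section, ten in the data collection section, so both are shown.

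**Assumed.** The village ICC, v, is not in the protocol. The range 0.005 to 0.05 is used, taken as part of the 0.13.

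**Step 1: the plan's own figures.** A one-sided, continuity-corrected comparison of 11.6% with 9.1% at 80% power needs 1,914 observations per arm. 1,914 × 1.50 / 5 = 574.2, which matches the stated 575 (with no allowance for drop-out in that figure). The stated 99% power for Arm 1 vs 3 also reproduces: at 600 per arm with 10% loss it is 99.8% one-sided and 99.6% two-sided. The sizing is thus built on the within-child correlation alone.

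**Step 2: formulas.** In units of p(1−p), the variance of a child's mean is t = (1 + (m−1) × 0.13)/m.
- Five visits: t = 1.52/5 = 0.304.
- Ten visits: t = 2.17/10 = 0.217.

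If the arms are balanced within villages, the contrast really carries t − v, while the child-clustered standard error still uses t. With S = 0.116 × 0.884 + 0.091 × 0.909 = 0.1853 and d = 0.025:
- planned SE = √(S × t/540); true SE = √(S × (t − v)/540)
- true two-sided error = 2 × (1 − Φ(1.96 × planned SE/true SE))
- power as planned = Φ((d − z × planned SE)/true SE)
- power adjusted = Φ(d/true SE − z), with z = 1.96 (two-sided) or 1.645 (one-sided)

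Worked example, m = 5 and v = 0.02: planned SE = √(0.1853 × 0.304/540) = 0.01021; true SE = √(0.1853 × 0.284/540) = 0.00987; ratio 1.035. Power as planned = Φ((0.025 − 0.02002)/0.00987) = Φ(0.505) = 69.3%. Power adjusted = Φ(2.533 − 1.96) = Φ(0.573) = 71.7%.

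**Step 3: Arm 1 vs 2, five visits, arms balanced within villages.**

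| Village ICC (assumed) | SE too wide by | True two-sided error | Two-sided power, planned → adjusted | One-sided power, planned → adjusted |
|---|---|---|---|---|
| 0.005 | 0.8% | 4.8% | 68.9 → 69.4% | 79.1 → 79.5% |
| 0.01 | 1.7% | 4.6% | 69.0 → 70.2% | 79.3 → 80.1% |
| 0.02 | 3.5% | 4.3% | 69.3 → 71.7% | 79.7 → 81.3% |
| 0.05 | 9.4% | 3.2% | 70.3 → 76.4% | 81.0 → 84.9% |

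With ten visits the SE excess runs from 1.2% to 14%. Two-sided power goes from 83.1 to 84.3% at ICC 0.01, 83.7 to 86.0% at 0.02 and 85.7 to 91.0% at 0.05.

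**Step 4: Arm 1 vs 3.** With d = 0.049 and S = 0.14 × 0.86 + 0.091 × 0.909 = 0.2031, even at ICC 0.05 the two-sided change is only from 99.8 to 99.9% (five visits).

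**Step 5: what if blocks do not balance villages?** In simulation (60 villages of 30 households assumed, five visits, ICC 0.005 to 0.05), balanced allocation gave a ratio of mean SE to true SE of 1.00 to 1.08 and two-sided error of 4.8% down to 3.4%. Unrestricted allocation gave ratios of 0.98 to 1.01 and error of about 5%. In a separate simulation, adjusting for village was no worse at ICC 0.02 and gained roughly 5 to 6 points at ICC 0.05, whether or not allocation balanced the arms.

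**Step 6: stratifying by block instead.** If blocks were of three (an assumption), each two-arm stratum would hold one child per arm, and with 10% loss only 600 × 0.9 × 0.9 = 486 pairs would be complete. At ICC 0.02, power = Φ(0.025/√(0.1853 × 0.284/486) − 1.96) = Φ(0.443) = about 67%, below the unadjusted 69.3%.

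**The case against.** The strongest reply is that nothing in the planned test is wrong. One household per bari is randomised and one target-age child per tubewell is assumed, so robust standard errors over a child's visits give a valid test that is at worst conservative. Whether to add village terms for precision is often settled in a statistical analysis plan, which is not at hand. The village ICC is assumed; 0.05 would make village 0.05/0.13 = 38% of the whole within-child correlation. Power is also not lost against plan: the unadjusted 69 to 70% compares with 68.7% when there is no village effect.

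Most of this stands, and it limits the point to an optional improvement. What remains is that the protocol does state its primary standard-error method, and that method leaves out information the trial already holds.

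Two stronger readings are tempting, and the protocol supports neither.
- A reader might infer that the standard errors are too wide as a matter of fact. That needs blocks lying within villages and village variance above zero; the protocol establishes neither.
- A reader might infer the reverse, that village sampling makes the primary standard errors too narrow. Because households and not villages are randomised, leaving out village did not make them materially too narrow in any simulated case.

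**Conclusion.** The planned primary test is sound for children of six months to two years, and no excess of false positives arises. It is less precise than it could be. How much less depends on an unstated village ICC: with five visits and arms balanced within villages, 0.5 to 2.4 points of two-sided power for Arm 1 vs 2 at assumed ICCs up to 0.02, and about 6 points at 0.05. On the one-tailed basis the trial was sized on, the range is 0.4 to 4 points. The main hypothesis is hardly touched. The statement that intervals are too wide and error is below 5% holds only if blocks balance the arms within villages.

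It should not be carried over to the under-five repeat analysis. There, siblings share one randomised household, and clustering on the child alone can make standard errors too narrow. For an assumed 1.2 to 2 children per household and a sibling correlation of 0.05 to 0.2, the factor √(1 + (k−1)ρ) runs from √1.01 = 1.005 to √1.2 = 1.095.

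**What to change.** In Data Analysis, estimate each of the three risk ratios adjusted for or stratified by village, using a Mantel-Haenszel risk ratio or a log-link Poisson model with village terms. Keep the robust standard errors for repeated visits and retain the unadjusted ratio as a sensitivity analysis. State the block size and whether blocks were formed within villages. Stratify by randomisation block only if blocks hold several children per arm.

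The cost is wording only; village should be known for every household from the sampling frame. Villages with no diarrhea in either compared arm contribute no information, and the gain is negligible if the village ICC is near zero. For the under-five repeat, cluster on the household instead of the child.

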**Data Collection:** There will be one baseline visit and ten follow-up visits to participating households.

Baseline Visit: We will conduct a baseline survey including demographics, household description, socioeconomic status, pre-intervention water, sanitation and hygiene habits and baseline levels of diarrhea in children between the ages of six months and two years. If there are any children in a recruited household that are between the ages of two and five, we will collect diarrhea data on them as well to allow comparison of our results to other findings in the literature that focus on children under the age of five. During the baseline visit, we will assess the microbial quality of the tubewell and stored water for each study household using the hydrogen sulphide (H2S) test. Tubewell and stored water samples from a subset of 150 households (50 from each study arm) will be analyzed for total coliforms and E. coli using membrane filtration.

Follow-Up Visits: Every month a field research assistant will visit each participating household to conduct a follow-up survey and collect information on the prevalence of diarrhea among children between the ages of six months and five years in the 48 hours as well as seven days preceding the visit. We are using a 48-hour recall because this typically provides a more valid estimate than longer recall periods which lead to under-reporting of health outcomes (Alam et al., 1989, Ramakrishnan et al., 1999, Feikin et al., 2010). We are also using a seven-day recall because recent findings indicate that while this longer recall period leads to only minimal bias in terms of the accuracy of recall it can result in significant gains of statistical power (Arnold et al., 2011).We will visit households once every month, because more frequent visits provide little additional statistical power due to correlation of repeated measures on the same individuals (Schmidt et al., 2007).

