## Data Analysis

Describe plans for data analysis. Indicate whether data will be analysed by the investigators themselves or by other professionals. Specify what statistical software packages will be used and if the study is blinded, when the code will be opened. For clinical trials, indicate if interim data analysis will be required to determine further course of the study.

The primary outcome will be longitudinal prevalence of diarrhea among children between the ages of six months and two years. If there are any children in a recruited household that are between the ages of two and five, their diarrhea outcome will be considered as well. We will use longitudinal prevalence because it is more strongly associated with malnutrition and mortality than is diarrhea incidence (Morris et al., 1996). We will collect diarrhea over 1 day, 2 day and 7 day recall periods. We will use a 7 day recall period to increase statistical power (Schmidt et al. 2010) if we confirm that the ratio of diarrhea cases in the past 24 hours (1 day recall) to cases that terminated between days 2-7 (the CT ratio) does not differ by randomized treatment group (Boerma et al. 1991). If the CT ratio differs by treatment group, it will indicate differential recall bias and so we will use a more conservative 2 day recall period in our primary analysis. Using STATA and/or SAS for data analysis, we will make the following three comparisons:

- Group 1 vs. 2: We will compare the longitudinal prevalence of diarrhea among children between the ages of six months and two years in households that receive chlorine water treatment and safe storage to households that receive safe storage. This will assess the contribution of water disinfection (separate from safe storage) to any reduction in diarrhea.
- Group 2 vs. 3: We will compare the longitudinal prevalence of diarrhea among children between the ages of six months and two years in households that receive safe storage only to households that receive no intervention. This will assess the effect of safe storage.
- Group 1 vs. 3: We will compare the longitudinal prevalence of diarrhea among children between the ages of six months and two years in households that receive chlorine water treatment and safe storage to households that receive no intervention. This will assess the combined effects of safe storage and disinfection.

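### Households are randomized but standard errors are clustered on the child, so the under-five analysis will probably report intervals that are too narrow

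*Protocol*

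**What the plan says.** The randomized unit is the household. Under Selection of Households (Research Design and Methods) the protocol states: "Recruited households will be randomized into one of the three study arms by block randomization". Where a bari contains several eligible households, "one of the households will be randomly selected and the primary caregiver in the selected household will be recruited", so each bari contributes one household.

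The Data Analysis section tests the risk ratios "using robust standard errors that account for repeated observations within children". The child is the only level of dependence it names for diarrhea.

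The same plan brings in more children from the same households. The Baseline Visit paragraph says: "If there are any children in a recruited household that are between the ages of two and five, we will collect diarrhea data on them". Data Analysis adds: "If there are any children in a recruited household that are between the ages of two and five, their diarrhea outcome will be considered". After describing the standard errors, that section continues: "We will repeat the calculations using the longitudinal prevalence of diarrhea among children under the age of five as the outcome measure".

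The sample size section assumes "1 child between the ages of six months and two years per tubewell", with an intraclass correlation of 0.13 and a design effect of 1.50, both for repeated measures on a child. Household dependence is acknowledged in one place only: Data Analysis plans generalized estimating equations for repeated water samples from one household.

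**The concern.** A cluster-robust variance treats different clusters as independent. If the cluster is the child, two children of one household count as independent pieces of evidence about the arm. They were assigned together by a single random allocation, drink the same stored water from the same tubewell, and live in the same surroundings. All of this points to positive correlation. Because both children are always in the same arm, the correlation adds to the variance of the between-arm comparison instead of cancelling out.

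The point estimate is not affected. What is at stake is the precision of the under-five risk ratios: intervals too narrow and P values too small. The protocol gives these results a definite use, comparison with published findings on children under five, and there the width of the interval matters.

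**Working it through.** **The plan's own figure.** With five visits and an intraclass correlation of 0.13, the design effect is 1 + (5 − 1) × 0.13 = 1.52, which agrees with the stated 1.50. It contains only the term for repeated visits and none for a second child in the household.

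**Inputs from the protocol.** Within-child correlation 0.13 (sample size section). Number of visits T: five in the sample size section and ten under Data Collection, so both are shown.

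**Inputs assumed, because the documents do not give them.** f, the share of households with one additional child under five: 0.3 to 0.5. ρ, the correlation between two children of a household, averaged over all pairs of visits: 0.03 to 0.10.

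**Formulas.** With prevalence p, the mean of one child's T visits has variance p(1 − p) × v, where v = [1 + (T − 1) × 0.13] / T.
- T = 10: v = 2.17 / 10 = 0.217
- T = 5: v = 1.52 / 5 = 0.304

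The means of two children in one household have correlation ρ / v. With m children per household, the true variance relative to the child-clustered variance is

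1 + (ρ / v) × (Σm² / Σm − 1), where Σm² / Σm − 1 = 2f / (1 + f).

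For f = 0.5 the last factor is 0.667; for f = 0.3 it is 0.462. The true two-sided type I error of a nominal 5% test is 2 × [1 − Φ(1.96 / √inflation)].

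**Results.**

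| Visits | f | ρ | Variance inflation | SE ratio | Interval too narrow by | True type I error |
|---|---|---|---|---|---|---|
| 10 | 0.3 | 0.03 | 1.064 | 1.031 | 3.0% | 0.057 |
| 10 | 0.5 | 0.05 | 1.154 | 1.074 | 6.9% | 0.068 |
| 10 | 0.5 | 0.10 | 1.307 | 1.143 | 12.5% | 0.086 |
| 5 | 0.3 | 0.03 | 1.046 | 1.023 | 2.2% | 0.055 |
| 5 | 0.5 | 0.05 | 1.110 | 1.053 | 5.1% | 0.063 |
| 5 | 0.5 | 0.10 | 1.219 | 1.104 | 9.4% | 0.076 |

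For example, the third row is 1 + (0.10 / 0.217) × 0.667 = 1.307.

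**Wider range.** With f from 0.2 to 1.0 and ρ from 0.02 to 0.13, ten visits give intervals 1.5% to 21% too narrow and a type I error of 0.054 to 0.121. Five visits give 1% to 16% and 0.053 to 0.101.

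**Simulation.** The log risk ratio was simulated with 540 households per arm (600 less 10% drop-out), five visits, 12% prevalence in both arms and 3,000 runs per setting.
- One child per household: the two kinds of standard error were identical, and rejection rates were 0.050 and 0.052 in the two settings tried.
- Half the households with a second child, household share of the latent variance 0.2: the household-clustered standard error was 1.09 times the child-clustered one. The null was rejected in 0.073 of runs with child clustering and 0.049 with household clustering.
- Household share lowered to 0.1: ratio 1.04, rejection rates 0.055 and 0.048.

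The simulation error of these rates is about √(0.05 × 0.95 / 3000) = 0.004. The last excess over 5% is therefore not distinguishable from chance, while the 0.073 clearly is.

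**The case against.** Four points can be made for the plan as it stands.

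- **The primary analysis is essentially unaffected.** The design assumes one target-age child per tubewell and recruits one household per bari, and all three planned comparisons are defined on children aged six months to two years. Two such children in one household are possible but should be uncommon. This stands.
- **The affected analysis is supplementary.** No hypothesis, sample size or power statement rests on it, and its point estimates do not change. This also stands, and limits how serious the matter is.
- **The wording names no cluster variable.** Household clustering also accounts for repeated observations within a child, so an SAP could adopt it without contradicting the protocol. This is true, but clustering on the child is the natural reading. The same section names the household when it deals with repeated water samples and omits it for diarrhea.
- **The size rests on assumed inputs, and the upper end is demanding.** A correlation of 0.10 across all pairs of visits, against 0.13 within a child, means that another child in the household predicts a child's diarrhea 0.10 / 0.13 = 77% as well as that child's own other visits. If 0.10 held only at the same visit and 0.03 otherwise, the average over ten visits would be (0.10 + 9 × 0.03) / 10 = 0.037. With f = 0.5 the inflation would then be 1 + (0.037 / 0.217) × 0.667 = 1.11 and the type I error about 0.063. This is a fair caution about size. It does not reverse the direction.

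**Conclusion.** The concern holds. As written, the level at which dependence is handled is below the unit of randomization, and the protocol carries that choice into an analysis that adds further children from the same household. Standard errors there will be understated if children of one household are positively correlated, which is expected although not documented.

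Under the main assumptions with ten visits, the understatement is 3% to 12.5% and the true type I error 5.7% to 8.6%. A middle case gives about 7% and 6.8%. If few households have a second child or the correlation is low, the effect is only 1% to 5%. The problem is practically confined to the under-five analysis; the primary analysis is touched only by the occasional household with two target-age children. It should be corrected, but it does not threaten the trial's main comparison.

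**What to change.** In Data Analysis, state that the robust standard errors for every diarrhea risk ratio are clustered on the household, the randomized unit, and say explicitly that this applies to the under-five analysis as well.

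Clustering on the household allows for any dependence among visits of one child and among children of one household. It gives the same result as child clustering wherever a household has one child. With 600 households planned per arm, each comparison has 1,200 clusters, ample for a robust variance.

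The cost is one reworded clause and one software option. No new data are needed, and the sample size and point estimates stay as they are. The under-five intervals become somewhat wider, by the SE ratio in the table above (about 1.02 to 1.14 under those assumptions).
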